#### **Grade 2 (Localized Urticaria)**

Subjects may continue the intake of investigational medication or have their investigational medication discontinued at the investigator's discretion. Subjects may continue treatment with PegIFN $\alpha$ -2a or RBV at the investigator's discretion. Close clinical follow-up is recommended to monitor for any progression of the AE. Subjects should be advised to contact the investigator immediately if there is any worsening of symptoms, in which case the subject will permanently discontinue the study medication. Rechallenge is not allowed.

#### **Grade 3 (Generalized Urticaria, Angioedema) and Grade 4 (Anaphylaxis)**

Subjects will immediately and permanently discontinue the intake of study medication. Rechallenge is not allowed. Subjects will be treated as clinically appropriate and should be followed until resolution of the AE.

Refer to Table 2 for an overview of the management scheme in case of an allergic reaction.

**Table 2: Guidelines for Subjects Developing Allergic Reactions**

| WHO Toxicity Grade | Definitions                                              | Investigator Action                                                                                                                                                                                                                                                          |
|--------------------|----------------------------------------------------------|------------------------------------------------------------------------------------------------------------------------------------------------------------------------------------------------------------------------------------------------------------------------------|
| Grade 1            | Pruritus suggestive of an allergic reaction without rash | May continue investigational medication (TMC435) or have their investigational medication (TMC435) discontinued at the investigator's discretion.
May continue treatment with PegIFN $\alpha$ -2a or RBV at the investigator's discretion.                                |
| Grade 2            | Localized urticaria                                      | May continue investigational medication (TMC435) or have their investigational medication (TMC435) discontinued at the investigator's discretion.
Rechallenge is not allowed.
May continue treatment with PegIFN $\alpha$ -2a or RBV at the investigator's discretion. |
| Grade 3            | Generalized urticaria, or Angioedema                     | Permanently discontinue study medication (TMC435, PegIFN $\alpha$ -2a and RBV) (see Section 10.2).                                                                                                                                                                           |
| Grade 4            | Anaphylaxis                                              | Permanently discontinue study medication (TMC435, PegIFN $\alpha$ -2a and RBV) (see Section 10.2).                                                                                                                                                                           |

### 9.5.7.3. AST and ALT and/or Bilirubin Elevation

Although an AST and ALT elevation of up to grade 3 is common in chronic HCV due to disease activity, treatment-emergent changes from baseline in ALT and AST levels should be carefully evaluated and closely monitored with unscheduled visits if needed. Increases in bilirubin (both direct and indirect) have been observed during the first weeks of TMC435 therapy. The bilirubin elevations are caused by a benign competitive inhibition of biliary transporter systems in hepatocytes. Bilirubin elevations following initiation of TMC435 therapy are typically not associated with increases in ALT/AST levels and rapidly resolve after completion of TMC435 treatment.

Management of treatment-emergent AST and ALT and/or bilirubin elevations will take into account the following protocol-defined procedures (see also Table 5 and Table 6 below).

In case the investigational medication is discontinued due to increased AST/ALT or bilirubin levels, PegIFN $\alpha$ -2a and RBV therapy may be continued at the investigator's discretion if the increased values are not signs of liver decompensation, but in subjects with progressive ALT increases, the dose of PegIFN $\alpha$ -2a should be reduced to 135  $\mu$ g and more frequent monitoring of liver function should be performed in line with the manufacturer's prescribing information.

**Table 3: Treatment-emergent Grade 1 to Grade 3 ALT or AST elevation or Grade 1 to Grade 3 total bilirubin elevation**

| WHO Toxicity Grade | AST or ALT, Ranges              | Total Bilirubin, Ranges        |
|--------------------|---------------------------------|--------------------------------|
| Grade 1            | $\geq 1.25$ to $\leq 2.5$ x ULN | $\geq 1.1$ to $\leq 1.5$ x ULN |
| Grade 2            | $> 2.5$ to $\leq 5.0$ x ULN     | $> 1.5$ to $\leq 2.5$ x ULN    |
| Grade 3            | $> 5.0$ to $\leq 10.0$ x ULN    | $> 2.5$ to $\leq 5.0$ x ULN    |

Subjects may continue intake of investigational medication or have their investigational medication discontinued at the investigator's discretion. Close clinical follow-up is

recommended to monitor for any progressive increase in ALT/AST or bilirubin levels. In order to continue the study medication, in case of a grade 3 ALT/AST increase, this laboratory abnormality must be judged by the investigator to be either “not related” or “doubtfully related” to the investigational medication. The investigational medication may be continued upon agreement with the sponsor.

**Table 4: Treatment-emergent Grade 4 ALT or AST elevation or Grade 4 total bilirubin elevation**

| WHO Toxicity Grade | AST or ALT, Ranges | Total Bilirubin, Ranges |
|--------------------|--------------------|-------------------------|
| Grade 4            | > 10.0 x ULN       | > 5.0 x ULN             |

If the grade 4 ALT/AST value is > 2 x baseline value, a confirmatory measurement should be performed within 72 hours after receipt of the results. In case of a confirmed value, the investigational medication should be discontinued.

For isolated grade 4 bilirubin values, subjects should have a confirmatory measurement within 72 hours after receipt of the results. In case of a confirmed grade 4 value, the investigational medication should be discontinued. Treatment with PegIFN $\alpha$ -2a and RBV may be continued at the investigator’s discretion if the increased values are not accompanied by signs of liver decompensation. Subjects who have known Gilbert’s disease and experience isolated grade 4 elevated indirect bilirubin can continue the investigational medication at the investigator’s discretion.

For concurrent grade 4 ALT/AST elevations > 2 x baseline value and grade 4 bilirubin values, subjects should have a confirmatory measurement within 72 hours after receipt of the results. In case of confirmed grade 4 elevations, the investigational medication should be discontinued. Treatment with PegIFN $\alpha$ -2a and RBV may be continued at the investigator’s discretion if the increased values are not accompanied by signs of liver decompensation.

Subjects should be followed until return to predose baseline or stabilization of ALT/AST and/or bilirubin elevation.

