    - The subject experiences severe worsening of hepatic disease (see Section 9.5.7.4).
  - Subjects must discontinue investigational medication (TMC435) and may continue PegIFN $\alpha$ -2a and/or RBV alone if:
    - They require treatment with one of the medications included in the list of disallowed concomitant medications (see Section 8).
    - The subject experiences grade 4 ALT/AST elevations  $> 2 \times$  baseline value and concurrent grade 4 bilirubin values, and the ALT/AST and bilirubin values continue to meet grade 4 criteria at re-testing performed 72 hours after receipt of the results (see Section 9.5.7.3). Subjects who have known Gilbert's disease and experience isolated grade 4 elevated indirect bilirubin can continue the investigational medication at the investigator's discretion.
    - The subject experiences a grade 3 or 4 AE (other than the rash/allergic reaction AE mentioned above) or confirmed grade 3 or 4 laboratory abnormality (other than grade 3 isolated increases in AST/ALT or bilirubin) considered to be at least

possibly related to TMC435 (2 consecutive measurements no more than 72 hours after receipt of first results). This excludes AEs or laboratory abnormalities that are not considered to be at least possibly related to TMC435.

- There will be a post-treatment follow-up of 24 weeks after end of treatment. All AEs occurring at any time during the study (including the follow-up period) will be followed until satisfactory resolution (e.g., value back to baseline value) or stabilization (to be agreed upon in collaboration with the sponsor).
- If a subject withdraws from the study (i.e., withdrawal of consent), he/she maintains the option to participate in the safety follow-up procedures.

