| Grade 1
Grade 2
Grade 3 | $\geq 1.25$ to $\leq 2.5$ x ULN
$> 2.5$ to $\leq 5.0$ x ULN
$> 5.0$ to $\leq 10.0$ x ULN | May continue intake of investigational medication or have their investigational medication discontinued at the investigator's discretion.
Monitor for progressive increase in ALT/AST levels.
In order to continue the study medication, in case of a grade 3 ALT/AST increase, this laboratory abnormality should be considered "not related" or "doubtfully related" to the investigational medication. The investigational medication may be continued upon agreement with the sponsor.                                                                                                                                                                                                                                                                                                       |
| Grade 4                       | $> 10.0$ x ULN                                                                                 | May continue study medication or have study medication discontinued at the investigator's discretion if value is $< 2$ times the baseline value and the event is considered "not related" or "doubtfully related" to the study medication. Subjects who continue should be carefully evaluated and close follow-up is recommended to monitor for progressive increase in ALT/AST levels.
If the grade 4 ALT/AST value is $> 2$ x baseline value, a confirmatory measurement should be performed within 72 hours after receipt of the results. In case of a confirmed value, the investigational medication should be discontinued (see also Section 10.2). PegIFN $\alpha$ -2a and RBV may be continued at the investigator's discretion if increased values are not signs of liver decompensation. |

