### **10.2. Discontinuation of Study Treatment**

If a subject's study treatment must be discontinued before the end of the treatment regimen, this will not result in automatic withdrawal of the subject from the study.

At the discretion of the investigator, all study medication (TMC435, PegIFN $\alpha$ -2a and RBV) may be discontinued for any of the following reasons:

- An SAE occurs.
- The subject fails to comply with the protocol or study staff requirements.

All study medication (TMC435, PegIFN $\alpha$ -2a and RBV) must be discontinued for any of the following reasons:

- withdrawal of consent.
- The subject meets a virologic stopping criterion at Week 4 or 12 or experiences viral breakthrough at any time point during treatment (see Section 6.3).
- The investigator believes that for safety reasons (e.g., AE) it is in the best interest of the subject to discontinue study treatment.
- The subject becomes pregnant.
- A subject fails to comply with the contraception requirements (in female subjects; refer to Section 4.3).
- The subject experiences a grade 3 or 4 rash/allergic reaction (see Sections 9.5.7.1 and 9.5.7.2).
- The subject experiences severe worsening of hepatic disease (see Section 9.5.7.4).

Subjects must discontinue investigational medication (TMC435) and may continue PegIFN $\alpha$ -2a and/or RBV alone if:

- They require treatment with one of the medications included in the list of disallowed concomitant medications (see Section 8).

- The subject experiences grade 4 ALT/AST elevations  $> 2 \times$  baseline value and concurrent grade 4 bilirubin values and the ALT/AST and bilirubin values continue to meet grade 4 criteria at re-testing performed 72 hours after receipt of the results (see Section 9.5.7.3).
- The subject experiences a grade 3 or 4 AE (other than the rash/allergic reaction AE mentioned above) or confirmed grade 3 or 4 laboratory abnormality (other than grade 3 isolated increases in AST/ALT or bilirubin) considered to be at least possibly related to TMC435 (2 consecutive measurements no more than 72 hours after receipt of first results). This excludes AEs or laboratory abnormalities that are not considered to be at least possibly related to TMC435. Subjects who have known Gilbert's disease and experience isolated grade 4 elevated indirect bilirubin can continue the investigational medication at the investigator's discretion.

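### The TMC435 stop lists in sections 10.2 and 1.5.5 are laxer than section 9.5.7.3 for isolated confirmed grade 4 liver values judged not or doubtfully related

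*Protocol*

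**What the plan says.** The text under Table 4 in section 9.5.7.3 sets three grade 4 stops for TMC435, each after a repeat test.

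- **ALT/AST above twice baseline:** "In case of a confirmed value, the investigational medication should be discontinued".
- **Bilirubin alone:** "For isolated grade 4 bilirubin values, subjects should have a confirmatory measurement within 72 hours after receipt of the results"; a confirmed value again leads to stopping TMC435. Known Gilbert's disease with isolated indirect bilirubin is excepted.
- **Both together:** TMC435 is stopped on confirmation.

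None of the three depends on relatedness. Table 5 does use relatedness at grade 4, but only for values below "times the baseline value and the event is considered" not or doubtfully related. Above that level the table reads "In case of a confirmed value, the investigational medication should be discontinued (see also Section 10.2"). The grade 4 row of Table 6 carries the same stop for bilirubin and the same pointer to 10.2.

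Sections 10.2 and 1.5.5 list when TMC435 must be stopped while the other two drugs may go on. Their one liver-specific item requires grade 4 ALT/AST above twice baseline together with grade 4 bilirubin, where both "continue to meet grade 4 criteria at re-testing performed 72 hours after receipt of the results (see Section 9.5.7.3"). The next item covers confirmed grade 3 or 4 laboratory abnormalities "other than grade 3 isolated increases in AST/ALT or bilirubin) considered to be at least possibly related to TMC435", and then adds: "This excludes AEs or laboratory abnormalities that are not considered to be at least possibly related to TMC435".

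**The concern.** Tables 5 and 6 send the reader to section 10.2 for these very stops. A site that follows the pointer finds the combined stop, finds no matching stop for either isolated elevation, and finds a relatedness exclusion that section 9.5.7.3 does not have. If section 10.2 is used as the working checklist, TMC435 could be continued after a confirmed grade 4 liver value that the investigator attributes to something else.

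That attribution is plausible for ALT/AST. Section 9.5.7.3 itself says that elevations up to grade 3 are common from the HCV disease, and three drugs are given together. Section 1.2 names the liver as the main target organ of TMC435 in the repeated-dose nonclinical studies. The stake is therefore consistent application of a liver-safety rule, not the efficacy analysis.

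**Working it through.** No figure in the plan is involved, so the check is a side-by-side reading. The inputs are section 9.5.7.3 with Tables 5 and 6, and the TMC435 stop lists in 10.2 and 1.5.5. Three confirmed grade 4 patterns, each judged either way on relatedness, give 3 × 2 = 6 cases. Bilirubin cases exclude known Gilbert's disease with isolated indirect bilirubin, which may continue under all three sections.

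| Confirmed grade 4 pattern | Relatedness to TMC435 | 9.5.7.3 | 10.2 and 1.5.5 |
|---|---|---|---|
| ALT/AST > 2 × baseline, isolated | at least possible | stop | stop (general item) |
| ALT/AST > 2 × baseline, isolated | not or doubtful | stop | **not listed** |
| Bilirubin, isolated | at least possible | stop | stop (general item) |
| Bilirubin, isolated | not or doubtful | stop | **not listed** |
| Both together | at least possible | stop | stop (liver item) |
| Both together | not or doubtful | stop | stop (liver item) |

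The sections differ in 2 of the 6 cases.

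Three details support this reading.

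1. The general item exempts isolated liver increases only at grade 3, so isolated grade 4 values fall inside it and inside its relatedness limit. Section 10.2 also places the Gilbert's exception for isolated grade 4 indirect bilirubin in that item. In 1.5.5 the same exception sits in the combined item, where an isolated elevation does not belong.
2. Section 9.5.7.5 lets TMC435 continue after unrelated abnormalities, but its rules except the toxicities covered in 9.5.7.1 to 9.5.7.4. It does not bring relatedness into 9.5.7.3.
3. Table 5 uses relatedness for grade 4 values below twice baseline and not above. Its absence above that level looks intended.

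One timing difference goes with this. Section 9.5.7.3 asks for the repeat test within 72 hours of receiving the result. The liver item in both lists has it "at re-testing performed 72 hours after receipt of the results (see Section 9.5.7.3"), which can be read as a test at 72 hours and not by 72 hours.

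**The case against.** The lists state conditions that are sufficient for stopping: TMC435 must be stopped *if*, not *only if*. The exclusion limits its own item and does not cancel section 9.5.7.3. The liver item cites 9.5.7.3, and 1.5.5 names section 9.5.7 as the toxicity plan. A site that takes the stricter rule complies with everything. All of this stands. A reader might infer that 10.2 instructs sites to keep dosing, and the text does not support that.

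A reader might also infer that the lists miss isolated grade 4 values altogether. They do not: a value judged at least possibly related is already a mandatory stop under the general item.

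The verbs differ. Section 9.5.7.3 says TMC435 *should* be stopped, Tables 5 and 6 are titled as guidelines, and the lists say *must*. One could read two tiers: mandatory stops for combined or related values, and recommended stops for isolated unrelated ones. The protocol never states such tiers. Section 9.5.7.3 also uses *should* for the combined case, which the lists make mandatory, so the verb does not separate the tiers. The difference is still real and leaves the sponsor's intention open.

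The affected group is probably small. Sections 1.2 and 1.5.3 list raised bilirubin as an identified TMC435 reaction, so an unrelated judgment for isolated bilirubin should be uncommon. Section 10.2 also requires stopping all drugs when the investigator thinks safety calls for it, or on severe worsening of hepatic disease. These backstops reduce the risk, but they rest on clinical judgment and do not reproduce a fixed laboratory stop.

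**Conclusion.** The inconsistency is real and minor. Section 9.5.7.3 calls for stopping TMC435 in two situations that the lists in 10.2 and 1.5.5 do not require: confirmed isolated grade 4 ALT/AST above twice baseline, and confirmed isolated grade 4 bilirubin outside the Gilbert's exception. The gap exists only when the value is judged not or doubtfully related to TMC435.

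The conclusion rests on reading the missing relatedness condition in 9.5.7.3 as intended, which Table 5 and the carve-out in 9.5.7.5 support. The protocol gives no rate for either situation, so the number of subjects affected cannot be estimated. SVR12, alpha and power are unaffected.

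**What to change.** In sections 10.2 and 1.5.5:

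- State that 9.5.7.3 governs all ALT/AST and bilirubin elevations, and that the relatedness exclusion in the general item does not apply to them.
- List as TMC435 stops, regardless of relatedness, confirmed grade 4 ALT/AST above twice baseline (with or without grade 4 bilirubin) and confirmed isolated grade 4 bilirubin. Keep the exception for known Gilbert's disease with isolated indirect bilirubin, placed with the bilirubin stop in both lists.
- Change the liver retest from one done at 72 hours to one done within 72 hours of receiving the result.

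Use one verb for these stops in all three sections. Putting them in a mandatory list implies *must*, and the sponsor should confirm that this is what it means.

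The cost is a short amendment to the text and a clarification to sites. There is no statistical cost.

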**Table 5: Guidelines for Subjects Developing ALT/AST Elevations**

| WHO Toxicity Grade            | Ranges                                                                                         | Investigator Action                                                                                                                                                                                                                                                                                                                                                                                                                                                                                                                                                                                                                                                                                                                                                                                    |
|-------------------------------|------------------------------------------------------------------------------------------------|--------------------------------------------------------------------------------------------------------------------------------------------------------------------------------------------------------------------------------------------------------------------------------------------------------------------------------------------------------------------------------------------------------------------------------------------------------------------------------------------------------------------------------------------------------------------------------------------------------------------------------------------------------------------------------------------------------------------------------------------------------------------------------------------------------|
| Grade 1
Grade 2
Grade 3 | $\geq 1.25$ to $\leq 2.5$ x ULN
$> 2.5$ to $\leq 5.0$ x ULN
$> 5.0$ to $\leq 10.0$ x ULN | May continue intake of investigational medication or have their investigational medication discontinued at the investigator's discretion.
Monitor for progressive increase in ALT/AST levels.
In order to continue the study medication, in case of a grade 3 ALT/AST increase, this laboratory abnormality should be considered "not related" or "doubtfully related" to the investigational medication. The investigational medication may be continued upon agreement with the sponsor.                                                                                                                                                                                                                                                                                                       |
| Grade 4                       | $> 10.0$ x ULN                                                                                 | May continue study medication or have study medication discontinued at the investigator's discretion if value is $< 2$ times the baseline value and the event is considered "not related" or "doubtfully related" to the study medication. Subjects who continue should be carefully evaluated and close follow-up is recommended to monitor for progressive increase in ALT/AST levels.
If the grade 4 ALT/AST value is $> 2$ x baseline value, a confirmatory measurement should be performed within 72 hours after receipt of the results. In case of a confirmed value, the investigational medication should be discontinued (see also Section 10.2). PegIFN $\alpha$ -2a and RBV may be continued at the investigator's discretion if increased values are not signs of liver decompensation. |

